
### Study participants

#### Eligibility

We plan to enroll 315 participants on the study. To confirm eligibility, participants will complete an eligibility survey. Participants must meet the following criteria in order to enroll on the study: 1) have previously enrolled in CCSS, 2) age > 30 years old, 3) were treated with radiation to the abdomen, pelvis, spine, or total body irradiation, 4) no history of CRC, 5) no family history of CRC, 6) have not had a colonoscopy in the last 5 years or multitarget stool DNA test in the last 3 years, 7) have a smartphone, 8) reside in the United States, and 9) speak English.

#### Recruitment

We will recruit participants from the CCSS; there are currently 1139 CCSS participants who fulfill the eligibility criteria (Table 1) [17]. The St. Jude CCSS Coordinating Center will recruit batches of 20–50 participants every few weeks. We will randomly sample from a list of eligible CCSS participants; we are planning to oversample racial minorites. Those who meet inclusion criteria will be emailed an invitation letter. After 2 weeks, a mailed letter will be sent to non-responders. A CCSS phone interviewer will call potentially eligible cohort members who fail to respond to two invitation letters and invite them to participate. We will continue attempting to accrue subjects from the eligibility list until 315 participants have been randomized into the study.

**Table 1 Tab1:**
[figure not shown]
Characteristics of eligible CCSS participants (*n*=1139)

### Intervention

Figure 1 summarizes the intervention components that will be randomly assigned to each arm.

#### Electronic resources

The following downloadable, electronic resources were designed by the study team and will be available to all study participants via the study website (see Additional file 2):Survivorship Care Plan (SCP): an overview of past cancer treatment and screening recommendations personalized for the participantHow to Use the SCP: a one-page tip sheet for using the SCPPotential Benefits and Other Considerations of Colorectal Cancer Screening: an overview of important factors to consider when making a choice about CRC screeningTip Sheet: Applying for Health Insurance: a step-by-step process for applying for health insurance using the Health Insurance MarketplaceHow to Find a Primary Care Provider: tips for steps to take to find a PCPFinancial Assistance Options: contact information for various sources of financial assistance for CRC screeningLetter for Insurance Company: a letter for participants to share with their insurance company to help with coverage for CRC screening

The SCP will be personalized for each participant: the study team will generate a draft SCP using previously collected data from the CCSS, an advanced practice registered nurse (APRN) will review the SCP for errors, and the study manager will upload the SCP to the website.

#### Text-message intervention

Based on feedback from our PCP advisory board, comprised of 9 General Internists, Family Physicians and Gynecologists, and preliminary data from the EMPOWER study [32] which utilized a similar text-message intervention to encourage breast cancer screening, we designed a interactive text-message intervention via the Mosio texting platform (Fig. 2). The text-message intervention employs the Patient Activation Model, which suggests that activated patients are better prepared to participate in self-management [18].

**Fig. 2 Fig2:**
[figure not shown]
Text message content overview

The texts include questions to be answered by the participants, educational links, reminders to view the study resources via the CCSS myLTFU website, and links to four videos on important topics. The following videos ranged from 60 to 90 seconds in length and were scripted and filmed by the study team using Zoom: 1) The Importance of Regular PCP Appointments for Cancer Survivors, 2) Perspective from a Cancer Survivor, and 3) Expected Cost of a Colonoscopy or multitarget stool DNA test.

In addition, in collaboration with the video animation company Splainers, we created a 60-second video explaining the key attributes of both a colonoscopy and a multitarget stool DNA test. Based on how they answer the questions, participants will receive study texts for a duration of 2–11 months. The text message intervention was thoroughly tested and reviewed by the study team to ensure accuracy.

#### Primary care provider resources

Informed by PCP activation strategies used by other studies with a similar focus to increase cancer screening rates [13, 14], the study team created the following primary care provider resources:Cover Letter: summary of patient’s SCP, contact information for study teamExecutive Summary: overview of current CRC screening recommendationsFAQ Page: answers to common questions such as “How often should high-risk patients be screened for colorectal cancer?”Insurance Letter Template: a letter to share with a patient’s insurance company to help with coverage for CRC screening

The PCP resources will be faxed along with the baseline survey.

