### Conceptual framework

The ASPIRES study is guided by the Patient Activation Model [18], which suggests that activated patients are better prepared to participate in self-management. Patient activation is the degree to which an individual understands they must play an active role in managing their own health and health care, and the extent to which they feel able to fulfill that role [19]. Individuals with higher levels of patient activation are more likely to undergo screening [20]. Activation involves four stages: (1) believing that taking an active role as a patient is important; (2) having the confidence and knowledge necessary to take action; (3) taking action to maintain and improve one’s health; and (4) staying the course even under stress [18].

Although the Patient Activation Model is a vital component of our conceptual model, we will include other important variables, many of which are from the Health Belief Model [21, 22] and the Transtheoretical Model [23–27]. These variables include benefits and barriers to screening; implementation intentions; perceived seriousness of susceptibility to CRC; and self-efficacy.

The ASPIRES study is enhanced by direct health care provider activation. PCP activation is designed to increase provider knowledge about the high-risk status of childhood cancer survivors and national screening recommendations, improve the motivation to discuss with, and order testing for, their patients, and facilitate effective information exchange and communication [28, 29]. We will examine specific factors (i.e., years in practice, location, knowledge) that may impact PCP activation.

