## Methods

### Study design

We will use a hybrid type II effectiveness and implementation design [30], to study the intervention’s effectiveness while also identifying facilitators and barriers to the implementation of the intervention [31]. While the University of Chicago will manage the study, our partners will play key roles. Memorial Sloan Kettering Cancer Center collaborators will conduct much of the data analysis, Columbia University colleagues will lead the cost and cost-effectiveness analysis, and the CCSS Coordinating Center partners at St. Jude Children’s Research Hospital will lead participant recruitment, administer the electronic informed consent process (see Additional File 1), create a study website for participants within their previously established personal study portal, and implement a messaging plan to communicate key study components to participants.

Participants will be randomized to one of three arms; the Best Practices Control (C) arm receives electronic educational resources (see Additional File 2) via the study website, the C + Patient Activation (PA) arm receives electronic educational resources via the study website as well as interactive text messages with links to videos and resources, and the C + PA + PCP Activation arm receives electronic educational resources via the study website, interactive text messages with links to videos and resources, and their PCPs are faxed educational materials (Fig. 1). For the purposes of this study, a PCP refers to a primary care provider or some other health care provider who the survivor sees regularly for care and who can order health screenings. Randomization will be stratified by age at study enrollment (30–44 and ≥ 45 years). We will use a permuted block randomization scheme with a random block size ranging from 6 to 12. The study principal investigators will be blinded to arm assignment.

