**Fig. 1 Fig1:**
[figure not shown]
ASPIRES STUDY flow diagram

Participants will be in the study for up to 15 months. All participants will complete a baseline and 12-month questionnaire via the CCSS Long-Term Follow Up study website (“My LTFU”). After completion of each of these questionanires, a participant will receive a $50 Amazon giftcard. A sample of 20 participants from each intervention arm will be invited to take part in an interview within 3 months after the completion of the 12-month questionnaire (see Implementation Outcome section below for more details). These interviewees will each receive a $50 Amazon giftcard. The primary care provider of each participant will complete a faxed baseline and 12-month questionnaire which include items to measure PCP activation, demographics, experience and comfort level providing care to cancer survivors, and knowledge about the healthcare needs of childhood cancer survivors; the 12-month questionnaire also includes CFIR items to aid in the evaluation of the implementation process. The PCPs will receive a $25 Amazon giftcard for completion of the baseline questionnaire, and a $50 Amazon giftcard for completion of the 12-month questionnaire. To gather additional data regarding the implementation process, we will also ask one medical office staff member associated with each participant’s PCP to complete a 12-month questionnaire via the phone. The medical office staff members will each receive a $25 Amazon giftcard for completion of the questionnaire. A sample of 20 primary care providers and 20 medial office staff from each intervention arm will take part in an interview within 3 months after the completion of the12-month questionnaire. Each interviewee will receive a $50 Amazon giftcard. We will identify each participant’s primary care provider by including a required section on the baseline questionnaire for participants to provide their PCP’s name and contact information. Similarly, the contact information for one medical office staff member working with each PCP will be collected via the baseline survey completed by each PCP. Participants without a PCP will be provided with a resource to encourage them to find a PCP, and will be asked repeatedly throughout the study to provide the study team with contact information for their PCP if one has been identified. The current study was approved by the University of Chicago Institutional Review Board (IRB20–1247), St. Jude Children’s Research Hospital Institutional Review Board (IRB21–0901), Memorial Sloan Kettering Cancer Center Institutional Review Board (IRB21–446), and the Columbia University Institutional Review Board (IRB-AAAT9278).

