##### Moderators and mediators

Another secondary effectiveness outcome is the assessment of potential moderators and mediators [39]. In this study, the potential moderators include patient characteristics, such as age, gender, educational attainment, health insurance coverage, types of insurance, chronic health conditions, and race/ethnicity as well as PCP factors such as knowledge, years in practice, and practice setting. The potential mediators may include the patient’s perception of involvement in decision-making, health insurance coverage, and whether the patient reviewed the study resources and videos. We will measure these moderators and mediators via the patient questionnaires, PCP questionnaires, and previously collected data from the CCSS.

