#### Questionnaires

We will collect baseline and 12-month participant questionnaires, baseline and 12-month PCP questionnaires, and a 12-month medical office staff questionnaire. To develop the participant questionnaires, the study team compiled all items in existing instruments such as the PAM [33], PROMIS [36, 37], and BSI-18 [38]. The study team also included modified items from a mammography screening tool [35], items developed based on Aizen’s Theory of Planned Behavior [34], CFIR items developed with the input of an expert on the study PCP advisory board [16], and other items designed to capture all significant variables such as CRC screening completion, moderator and mediator data, and cost information.

To create the primary care provider questionnaires, the study team modified an 18-item survey which was previously administered to measure family physician knowledge regarding the care of childhood cancer survivors [14]. The study team edited this questionnaire to include CFIR items and questions to measure key demographic variables [16]. The medical office staff questionnaire was designed by the study team to gather additional feedback on the implementation of the intervention from the helpful perspective of a staff member working alongside the PCPs. All questionnaires were reviewed by the study PCP advisory board which includes many clinician-researchers, two psychologists, multiple primary care providers, a research nurse with expertise in CFIR, a cancer survivor/social worker, among other experts.

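### In the C + PA + PCP Activation arm the baseline PCP survey arrives with the educational materials, so PCP knowledge is not a valid pre-intervention moderator for comparisons involving that arm

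*Protocol article*

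**What the plan says.** All references are to the protocol article.

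- **Who gets the materials.** Under Study design, only in the C + PA + PCP Activation arm is it the case that "their PCPs are faxed educational materials".
- **Who is surveyed.** The text below Figure 1 covers all three arms: "The primary care provider of each participant will complete a faxed baseline and 12-month questionnaire". The listed content includes PCP activation, demographics, "experience and comfort level providing care to cancer survivors, and knowledge about the healthcare needs of childhood cancer survivors". Under Questionnaires, the study team says it "modified an 18-item survey which was previously administered to measure family physician knowledge regarding the care of childhood cancer survivors".
- **When the materials go out.** Under Primary care provider resources: "The PCP resources will be faxed along with the baseline survey". The packet holds a cover letter summarising the care plan, a summary of current CRC screening recommendations, an FAQ page (one example is the screening interval for high-risk patients) and an insurance letter template.
- **What the materials are for.** Under Conceptual framework: "PCP activation is designed to increase provider knowledge about the high-risk status of childhood cancer survivors and national screening recommendations".
- **How the measure is used.** Under Moderators and mediators, the potential moderators are patient characteristics "as well as PCP factors such as knowledge, years in practice, and practice setting", taken in part from the PCP questionnaires. The analysis section tests each moderator by logistic regression with a product term, using a likelihood-ratio comparison of nested models.

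**The concern.** A moderator analysis asks whether the intervention effect differs across levels of a characteristic that assignment could not have altered. Here one arm's PCPs can consult the screening summary and FAQ while they answer the knowledge items, and the other arms' PCPs cannot. The recorded score then means different things by arm: prior knowledge in C and C + PA, and prior knowledge plus whatever the packet added in C + PA + PCP Activation. A product term built on such a score can pick up the measurement difference instead of true effect modification.

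At stake is one named moderator within a stated secondary objective, in the arm that exists to test PCP activation. A later analysis plan cannot repair this, because the article fixes the delivery procedure and a pre-exposure value that was never collected cannot be reconstructed.

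**Working it through.** The plan gives no figure to reproduce on this point. The check is a side-by-side reading, followed by an illustration with assumed inputs.

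**1. Timing by arm**

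| Arm | Baseline PCP survey | Materials with that survey | Baseline knowledge score |
|---|---|---|---|
| C | yes | no | pre-exposure |
| C + PA | yes | no | pre-exposure |
| C + PA + PCP Activation | yes | yes, same fax | post-exposure, or at best uncontrolled |

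Nothing in the article requires the survey to be completed before the materials are read. The article does not say which survey wave supplies the moderator, but the 12-month wave is also post-intervention, so it does not help.

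**2. False-positive rate when there is no true moderation**

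- From the article: 315 / 3 = 105 per arm; about 20% screened in control; a 20-point difference targeted for each pairwise comparison, so about 40% with C + PA.
- Assumed: half of PCPs in the PCP arm read the fax; reading adds 0.5, 1.0 or 1.5 SD to the recorded score; every PCP returns a survey; true knowledge is standard normal and unrelated to screening; nominal 5% test.
- Model, PCP arm versus control: logit P = β0 + β1·arm + β2·score + β3·arm·score. Moderation is declared if the change in −2LL from dropping β3 exceeds 3.84.
- 6,000 simulated trials per setting. The Monte Carlo standard error at 10% is √(0.10 × 0.90 / 6000) = 0.4 points.

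| Screened in PCP arm: non-readers' / readers' patients | Arm mean | No shift | 0.5 SD | 1.0 SD | 1.5 SD | Mean spurious β3 (0.5 / 1.0 / 1.5 SD) |
|---|---|---|---|---|---|---|
| 20% / 60% | 40% | 5% | 9% | 21% | 31% | 0.20 / 0.36 / 0.45 |
| 40% / 60% | 50% | 6% | 7% | 9% | 10% | 0.10 / 0.17 / 0.20 |
| 40% / 50% | 45% | 5% | 6% | 7% | 6% | 0.06 / 0.09 / 0.10 |

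The arm mean is 0.5 × non-readers + 0.5 × readers. Repeat runs differ by about a percentage point, so I quote about 10–30% for the first row and about 6–11% for the other two. The first row sets non-readers' patients at the control rate, which gives texting no effect. The other rows give texting the 20-point effect the design assumes.

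**3. Direction**

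The sign can reverse. Assume control screening of 12% with low-knowledge and 32% with high-knowledge PCPs, and a common odds ratio of (0.40/0.60)/(0.20/0.80) = 2.67. The PCP arm then has 26.7% and 55.7%, and the true interaction is zero. Suppose 30% of PCPs are truly high and 25% of the rest score high because they hold the materials.

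- Recorded-high share: 0.30 + 0.70 × 0.25 = 0.475.
- Screening in that group: (0.30 × 0.557 + 0.175 × 0.267) / 0.475 = 0.450.
- Apparent interaction: [logit(0.450) − logit(0.32)] − [logit(0.267) − logit(0.12)] = 0.55 − 0.98 = −0.43.

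With 30–50% truly high and 25–75% of the rest misrecorded, the apparent interaction runs from −0.23 to −0.75.

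**The case against.** **The survey may not test what the fax teaches.** The source instrument concerns the care of childhood cancer survivors in general, the fax concerns CRC screening, and the items are not shown. A PCP might also answer before reading. This stands as a limit on size: the overlap is inferred from the described content. It does not restore the baseline, because raising provider knowledge is the stated aim of PCP activation and no procedure ensures the order.

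**The timing may be specified elsewhere.** Table 2, which carries data collection timing, is not shown, and the moderator's wave is not stated in the text. Neither available wave is pre-exposure in this arm if the fax is sent as described.

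**A single fax limits burden.** The Limitations section treats PCP participation as a challenge, and waiting for the survey delays the PCP component within a 12-month window. This is a fair cost, and the fix should cap the wait.

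**Stronger readings a reader might infer, and why they fail:**

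- *PCP knowledge cannot be used at all.* Baseline knowledge is unexposed in C and C + PA, so that comparison is untouched by the joint fax.
- *False moderation is likely to reach 30%.* This needs the whole arm effect to come through fax reading, against the article's own assumption for texting. It also assumes complete PCP response; with half responding, the same unfavourable inputs give 8%, 13% and 18%.
- *Knowledge will falsely look like a positive moderator.* The sign depends on assumptions, as shown above.
- *The baseline-to-12-month gain in PCP knowledge or activation will be understated.* The article plans no such change analysis and evaluates PCP activation from the 12-month questionnaire. Activation is not among the listed PCP moderators.
- *The primary result is compromised.* The primary outcome is participant self-report of screening and does not use the PCP survey.

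**Conclusion.** The point holds for one moderator and for comparisons involving one arm. PCP knowledge is measured after exposure in the C + PA + PCP Activation arm and before exposure in the other two, so an arm-by-knowledge interaction involving that arm cannot be read as effect modification by prior knowledge. The structural flaw follows from the article's own text and needs no assumed number.

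Its numerical effect does rest on assumptions: the share of PCPs who read the fax, the score shift, the response rate and how much of the arm effect runs through the fax. Under the inputs above, false moderation is about 6–11% if texting works as the trial is powered for and about 10–30% at the unfavourable extreme, against 5–6% with a clean baseline. The direction is not predictable. C + PA versus C, years in practice, practice setting, the primary outcome and its power are unaffected. This is a modest flaw in a secondary analysis, worth correcting because correction is cheap.

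**What to change.** **Preferred.** In the C + PA + PCP Activation arm, fax the baseline survey alone. Send the resources when it is returned or after a short fixed wait, whichever is earlier. Record the survey return date, and use for the moderator only surveys returned within that same window in all three arms, so that the rule does not itself differ by arm.

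**If the joint fax stays.** Drop PCP knowledge as a moderator for comparisons involving that arm and report it only descriptively or as a 12-month outcome by arm. Years in practice and practice setting can remain as PCP moderators throughout, and knowledge at baseline can remain for C + PA versus C.

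**Cost.** The preferred option costs a second fax in one arm and a slightly later start of the PCP component within the 12-month outcome window. The alternative costs one sentence in the analysis plan and the loss of one moderator for that arm. Neither needs more participants.

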### Outcome measures

Table 2 provides an overview of effectiveness and implementation outcomes, including operational definitions, data sources, and data collection timing details.

**Table 2 Tab2:**
[figure not shown]
Primary and Secondary outcome measures

#### Effectiveness outcomes

##### CRC screening rate

The primary effectiveness outcome is CRC screening completion within 12 months after randomization. CRC screening completion is defined as the proportion of participants who self-report obtaining a colonoscopy or multitarget stool DNA test (multitarget stool DNA test plus colonoscopy if multitarget stool DNA test is positive). A secondary effectiveness outcome is CRC screening completion by 12 months after randomization, as measured through medical record report confirmation. Study team members will reach out to retrieve a medical record report to confirm CRC screening for each participant who reports that screening was completed within 12 months of randomization.

Through participant questionnaire items, we will assess key factors which may be associated with CRC screening completion (Table 3). Participant activation will be measured through the Patient Activation Measure (PAM) short form [33]. PCP activation will be evaluated through targeted questions in the 12-month PCP questionnaire. Intention to have CRC screening will be measured through questionnaire items developed based on the Theory of Planned Behavior [34]. In order to evaluate the benefits and barriers to CRC screening and the perceived seriousness of susceptibility to CRC, we adapted questions from the Champion Benefits Scale for Mammography Screening [35]. We will use the Patient-Reported Outcomes Measurement Information System (PROMIS) questionnaire to measure self-efficacy [36, 37].

